### Frequency of analyses

The BALANCE Pilot Trial will be conducted and reported according to recommendations by the Consolidated Standards of Reporting Trials (CONSORT), including analyzing patients in the groups to which they were originally assigned (intention-to-treat) and explicit procedures for handling of any missing data [49].

Analyses will be conducted at the completion of this pilot, given that there is no role for early termination [50]. However, we will monitor recruitment and adherence rates weekly, and examine barriers as needed, working with participating centers to provide screening and consenting tips from prior CIHR-funded ICU trials [34]. Capturing a minimal dataset of patient, pathogen and bacteremia source characteristics among eligible nonenrolled patients will facilitate this, and comparisons with eligible patients will help to identify selection bias [49].

### Subgroup analyses

To inform and possibly refine the main BALANCE Trial design, we will perform four exploratory subgroup analyses. The main subgroup analysis will be based on the underlying infectious syndrome causing bacteremia (vascular catheter-related, pneumonia, pyelonephritis, intra-abdominal, skin and soft tissue, other identified source, or unknown source). We will also perform subgroup analyses based on illness severity (APACHE II score of ≥25 versus <25), community- versus hospital-acquisition, and vasopressor use on day of randomization. If recruitment rates or protocol adherence are particularly low for any subgroups, in consultation with the Steering Committee and CCCTG, we will consider modifying definitions or procedures appropriately. For safety analyses, we will perform a per-protocol analysis by restricting the analysis to the participants who adhered perfectly to the protocol in terms of the eligibility, interventions, and outcome assessment.

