### Statistical analysis

#### Sample size

To estimate our expected adherence rate of 90% within a margin of error of ± 5% (that is, actual adherence 85 to 95%), with 95% confidence, we plan to enroll 115 patients. At our expected recruitment rate of 1 patient/site month across 15 sites, we will need approximately 10 to 24 months to recruit these 115 patients given variability in site trial start-up steps (REB approval, data sharing agreements and contracts). By the time we have recruited 115 patients, we will know with 95% confidence that this number of sites would be able to recruit 95 to 138 patients over the same time interval in a future trial; this data will then be used to estimate the number of centers needed for the main trial (see Additional file 1 for detailed sample size calculation).

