### Data Safety and Monitoring Committee (DSMC)

After broad discussion and engagement of the CCCTG it was determined that a DSMC would not be required for this pilot study, given the short duration of enrolment, and that it is underpowered to examine mortality. A DSMC will be instituted for the subsequent main BALANCE trial [51]. DSMC composition will follow accepted norms of content expertise (critical care, infectious diseases, methodology, and biostatistics) and independence from the investigators and steering committee.

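### The exploratory severity subgroup is defined only by cutting APACHE II at 25; under a linear effect this gives up at least about a third of the score's information, and a pre-specified continuous term would recover it

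*Protocol article*

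**What the plan says.** The Subgroup analyses section of the protocol article opens with the purpose: "To inform and possibly refine the main BALANCE Trial design, we will perform four exploratory subgroup analyses". It ranks them: "The main subgroup analysis will be based on the underlying infectious syndrome causing bacteremia". Severity is one of the other three, next to place of acquisition and vasopressor use, and is defined in one clause: "We will also perform subgroup analyses based on illness severity (APACHE II score of ≥25 versus <25".

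The same section says how the results may be used. It begins "If recruitment rates or protocol adherence are particularly low for any subgroups, in consultation with the Steering Committee and CCCTG" and goes on to say that changes to definitions or procedures will be considered.

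The Sample size section sets the pilot at 115 patients: "with 95% confidence, we plan to enroll 115 patients", with adherence expected at 90%. On deaths, the section on the data safety and monitoring committee says of the pilot that "it is underpowered to examine mortality".

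Outside the subgroup clause and the abbreviation list, APACHE II does not appear. It plays no part in eligibility, in stratification (by ICU site only) or in the trial interventions.

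**The concern.** Of the four subgroup variables, severity is the only numeric score; the other three are categories by nature. Splitting it at 25 treats scores of 24 and 25 as different and scores of 25 and 40 as the same. The score has to be worked out to place a patient on either side of the cut, so the finer information exists for every patient who is classified.

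What is at stake is the pilot's ability to show a gradient in adherence with severity. At 90% adherence, 115 patients give about 115 × 0.10 = 11.5 non-adherent courses. With so few events, an analysis that gives up a third or more of the information in the explanatory variable is more likely to miss a real gradient, and the result also depends on where 25 falls in the recruited population.

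**Working it through.** **Inputs from the article.** Cut at 25, two groups; 115 patients; expected adherence 90%; exploratory status. **Not in the article, so assumed.** The shape of the APACHE II distribution, the share q of patients scoring 25 or more, and the form and size of any severity effect.

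**The plan's own figures.** The article gives no precision or power for the severity subgroup, so there is nothing of that kind to reproduce. The stated range of 95 to 138 recruits does reproduce: the exact Poisson 95% interval for a count of 115 is 94.9 to 138.0. The 115 itself does not follow from 90% ± 5%: 1.96² × 0.9 × 0.1 / 0.05² = 138.3, and at 115 the half-width is 1.96 × √(0.09/115) = 5.5 points. The detailed calculation is in an additional file that is not shown. This is a separate matter and does not change the percentage losses below, so 115 is used as given.

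**Information kept by the cut.** For a normal score with a linear effect, the fraction kept is φ(c)² / [q(1 − q)], where c is the standard normal point with a share q above it. For example, at q = 0.50, c = 0 and φ(0)² = 0.159, so 0.159 / 0.25 = 0.637.

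| Share scoring ≥25 | Kept | Lost | 115 × kept |
|---|---|---|---|
| 50% | 0.637 | 36.3% | 73 |
| 40% or 60% | 0.622 | 37.8% | 72 |
| 30% or 70% | 0.576 | 42.4% | 66 |
| 27% or 73% | 0.555 | 44.5% | 64 |
| 20% or 80% | 0.490 | 51.0% | 56 |
| 10% or 90% | 0.342 | 65.8% | 39 |

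The minimum, 1 − 2/π = 36.3%, occurs when 25 is the median.

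**Sensitivity to shape.** Right-skewed integer scores with assumed means of 18 to 28 and SDs of 7 to 8 gave losses of 36% to 45%.

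**Simulated checks, n = 115, all effect sizes assumed.**
- Arm-by-score interaction on a continuous outcome (slope difference 0.4 SD per SD): loss 37%, 46% and 53% with 50%, 30% and 20% above the cut. Power was 55% with the score and 38%, 34% and 30% with the cut.
- Adherence gradient (mean adherence 90%, odds ratio 0.5 per SD): power about 58% with the score and 36% to 42% with the cut. A second run gave about 56% against 34% to 40%.
- Arm-by-score interaction on mortality (25% mortality, interaction log odds ratio 0.8 per SD): power about 40% with the score and 24% to 28% with the cut.

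**When the result reverses.** The fraction kept is the squared correlation between the score and its two-group version, so it applies in both directions. If the true effect is a step near 25, the cut loses little or nothing and the linear term is the less efficient of the two.

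**The case against.** The strongest reply is that this is an exploratory analysis, not the main subgroup, with no power or precision claimed for it. The go/no-go criteria rest on recruitment per site and adherence within each arm, and neither uses APACHE II. That stands, and it keeps the point small.

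The stated use of the subgroups is also partly descriptive. Recruitment by severity is naturally a count per group, a continuous term does nothing for it, and a cut fixed in advance avoids a threshold chosen from the data. This stands as a reason to keep the two-group table. It is not a reason to have only that table, since a continuous term fixed in advance also avoids a data-driven threshold.

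A reader might infer more than the article supports:
- That a continuous analysis is ruled out. The article neither plans nor excludes one, and a fuller document may add it. What can be said is that the one severity analysis it does fix is the cut.
- That the loss is a known 36% to 45%. That range needs roughly 27% to 73% of patients at 25 or above, a near-normal score and a linear effect, and none of these is documented.
- That the score is complete for all patients. The article does not say so.
- That nothing could follow from a split at 25. Low adherence in either severity group could prompt changed definitions or procedures.

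Finally, 11 or 12 non-adherent courses are too few for a useful formal test of non-linearity. That is correct, and the fix below does not ask for one.

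**Conclusion.** The point holds as a modest improvement in efficiency; it is not an error or a contradiction. Assuming a roughly normal score and a roughly linear effect, cutting at 25 loses at least about 36% of the information in APACHE II, so 115 patients count for at most about 73. The loss is about 45% with 27% or 73% of patients at 25 or above, and about 51% with 20% or 80%. Under a threshold effect near 25 it would be small.

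The practical consequence is a weaker chance of seeing an adherence gradient with severity, which is something the pilot says it wants to learn. The adherence argument carries the point. The mortality interaction does not: even with the large assumed effect above, power is only about 40% with the full score, so either analysis would usually miss it. A reader might infer that the feasibility conclusion is at risk; it is not, because no feasibility criterion depends on severity.

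**What to change.** In Subgroup analyses, replace the severity clause with wording such as: *Illness severity will be explored with APACHE II as a continuous linear term. Adherence will be related to the score, and clinical outcomes will be examined through an arm-by-score interaction. Each will be reported as an estimate with 95% CI. Recruitment, adherence and outcomes will also be tabulated for scores of 25 or more and below 25, for description. Departure from linearity will be inspected graphically only.*

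Add a short reason for the value 25 if the table keeps it.

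The change needs no new patients, procedures or data beyond the score already required to form the groups. Its costs are slightly more analysis work and reliance on a linear effect. The retained table and the plot give only a limited check on that assumption.

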### Steering committee

The Steering Committee is responsible for development and oversight of the BALANCE Pilot and full RCT procedures and operations, funding applications, recruitment rates, missing data rates, in addition to advising the principal applicants on responses to questions from the data safety and monitoring committee or other stakeholders, and eventual interpretation and compilation of study results into reports, scholarly manuscripts and knowledge translation and exchange activities.

The steering committee will meet in-person thrice yearly at CCCTG meetings (November, Ontario; January, Alberta; June, Eastern Canada) and by teleconference as needed between meetings.

### Data Safety and Monitoring Committee (DSMC)

After broad discussion and engagement of the CCCTG it was determined that a DSMC would not be required for this pilot study, given the short duration of enrolment, and that it is underpowered to examine mortality. A DSMC will be instituted for the subsequent main BALANCE trial [51]. DSMC composition will follow accepted norms of content expertise (critical care, infectious diseases, methodology, and biostatistics) and independence from the investigators and steering committee.

## Discussion

### Rationale for studying bacteremia

Some might argue that duration of antibiotic treatment should be driven by the underlying infectious focus, rather than the presence or absence of bacteremia. However, in our national practice survey the distributions of treatment duration recommendations were virtually identical for scenarios of bacteremic pneumonia, bacteremic pyelonephritis, catheter-related bloodstream infection, bacteremic intra-abdominal infection, and bacteremic skin and soft tissue infection - highlighting that bacteremia is a very influential syndromic aspect and the appropriate focus for our research program [28]. The advantages of studying bacteremia as a clinical entity versus other associated syndromes outweigh any potential disadvantages. In contrast to syndromic diagnoses (ventilator-associated pneumonia for example), all patients with bacteremia have a positive sterile site culture result (by definition). Therefore, all bacteremic patients (with noncontaminant species) have true infection, whereas the presence or absence of pneumonia is much harder to define because cultures may represent colonization rather than infection, and even multiple adjudications of case definitions provide only moderate agreement, particularly in patients on mechanical ventilators [52,53]. Given that bacteremia is defined by the positive blood culture result, all study patients will have an identified pathogen, in contrast to syndromic infections, which are often treated empirically without a defined etiology. A corollary is that antibiotic susceptibility test results are available for all bacteremic patients, so it will be clear whether or not patients randomized to shorter versus longer duration antibiotic treatment are receiving an effective antibiotic. The bacteremic subgroups of patients with pneumonia, pyelonephritis, intra-abdominal infection, and soft tissue infection, generally have more severe and complicated courses than non-bacteremic infections. Therefore, if shorter course therapy is demonstrated to be effective for bacteremic patients, the results can be more easily generalized to non-bacteremic patients than vice versa. Finally, pre-specified subgroup analyses in the main BALANCE RCT can examine the impact of treatment duration within each specific syndrome.

### Rationale for studying fixed duration therapy versus individualized durations based on clinical or biomarker based stopping rules

Ideally antibiotic treatment duration should be individualized, and patients should be treated until their infection has been cured (and likely no longer) [24]. Unfortunately, a randomized controlled trial based on a clinical stopping rule is not feasible in ICU patients, because there are no specific markers of persistent infection during critical illness. The difficulty in diagnosing infection in ICU and monitoring clinical response to treatment, has generated considerable interest in the use of novel biomarkers to guide antibiotic treatment duration [42,54]. One biomarker, procalcitonin, has been used successfully to reduce average treatment durations in sepsis [42]. However, only a minority of these patients were bacteremic. Moreover, more than half of patients randomized to the procalcitonin group, were not given algorithm-guided treatment because the attending physician believed a biomarker-informed duration was inappropriate [54].

Instead, we favor a randomized trial of fixed shorter versus longer duration antibiotic therapy, guided by our preliminary studies, as the most easily transferrable result to immediately inform clinical practice. This approach has been successful in more than two dozen randomized controlled trials of infectious diseases that are potentially complicated by bacteremia [21]. Most notably, a trial in ventilator-associated pneumonia has altered the standard of care for this infection to shorter duration therapy (8 days) [19]. However, appreciating the future promise of individual patient focused biomarkers to further nuance treatment decisions, we will measure procalcitonin levels and trajectory in both treatment arms to see if it could provide incremental prognostic value [49].

## Trial status

The study protocol is approved by the Sunnybrook Health Sciences Centre and Kingston General Hospital REBs. Funding has been obtained for this pilot RCT from the Ministry of Health and Long-Term Care Academic Health Sciences Alternative Funding Plan Innovation Fund Award (Ontario, Canada). The case report forms (paper and electronic) have been finalized. Training will be done for all the participating sites through webinar before starting recruitment. The study is registered with randomize.net and randomization of test patients has been successfully achieved. The trial is expected to begin enrolling patients in October 2014. Recruitment of patients will start at Sunnybrook Health Sciences Centre (coordinating center) and then roll out successively to the other sites after obtaining REB approval at the individual sites, and finalizing data sharing agreements. With the planned recruitment, we expect to complete this pilot trial in the summer of 2016 and then enroll further Canadian and International centers for the main BALANCE RCT. If the pilot RCT does not identify a need for any substantive protocol changes, this will be an internal pilot trial, and patients will be rolled into the main trial.

## Abbreviations

APACHE: Acute physiology and chronic health evaluation
CCCTG: Canadian critical care trials group
CIHR: Canadian institutes of health research
CLSI: Clinical laboratory & standards institute
CONSORT: Consolidated standards of reporting trials
DSMC: Data safety and monitoring committee
ICU: Intensive care unit
ID: Infectious diseases
RCT: Randomized control trial
SDM: Substitute decision maker
